### Statistical analysis

The data will be summarized with descriptive statistics (mean, median, standard deviation, percentiles for numerical variables, frequencies and percentages for categorical variables). The SPSS software version 26 will be used to analyze the data. The Shapiro–Wilk test will be used to examine the normal distribution of data. If the normal distribution is approved, the mix model ANOVA will be used to compare the differences in scores related to each variable in the pre-test and post-test in each group (with-in group effects) and to examine the differences between groups in each time point (between group effects), and Bonferroni post hoc test will be used to find significant differences and compare the groups. This model allows for possible missed data. We will assume data missing at random. Study group and time of assessment will be used as fixed factors and patients will be used as random factors. Otherwise, the Mann–Whitney *U* test will be used to compare two independent groups in case the normal distribution was not approved. Finally, after post hoc tests, the Cohen test (*d*) will be used in order to calculate the effect size [24]. *P*-value < 0.05 will be considered significant. The main conclusion will be drawn from the unadjusted analysis without performing any subgroup analysis of primary and secondary outcomes.

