## Aims

Primary aim: Investigating the effect of a patient-led goal-setting approach and PNE compared with a patient-led goal-setting approach and MT on pain intensity, disability, and quality of life in patients with chronic LBP.

Secondary aim: Investigating the effect of a patient-led goal-setting approach and PNE compared with a patient-led goal-setting approach and MT on psychological factors in patients with chronic LBP.

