### Description of the control

Participants in the control group will receive no specific intervention. However, for meeting the ethical codes, we will provide the patients in the control group with a pamphlet included with useful information on taking care during chronic LBP.

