## Discussion

The aim of this study will be to compare the effect of patient-led goal-setting approach combined with PNE or MT in patients with chronic LBP. The main question of this study is whether the patient-led goal-setting approach combined with PNE is more effective than MT in reducing pain intensity related with chronic LBP. Further objectives will be also to assess the effect of these two interventions on disability, quality of life, and psychosocial factors in chronic LBP compared to a control group. A total of 105 patients will participate in this study and the athletic trainer who performs the pre-test and post-test as well as follow-up evaluations will be blinded to the participants’ group code. It is expected that this RCT will provide novel data on the effectiveness of the patient-led goal-setting approach combined with PNE or MT in patients with chronic LBP compared to a control group.

In the current study, we will evaluate the effects of combined interventions on psychological outcomes as well as central sensitivity. It is expected that this prospective trial may contribute towards refining guidelines for good clinical practice and may be used as a basis for health authorities’ recommendations. If successful, the findings and information provided by this study will potentially have implications for physiotherapists, athletic trainers, and health care practitioners.

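### The trial's question is PNE versus MT, but the Bonferroni post hoc rule gives that contrast no priority over the control pairs; this is valid but needlessly conservative, costing about 7 to 18 points of power where it applies

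*Protocol article*

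**What the plan says.** The Aims section of the protocol article has two aims, and both name a single contrast. The primary aim is "Investigating the effect of a patient-led goal-setting approach and PNE compared with a patient-led goal-setting approach and MT on pain intensity, disability", with quality of life as a third outcome; the secondary aim is the effect of goal setting plus "PNE compared with a patient-led goal-setting approach and MT on psychological factors in patients with chronic LBP". The Discussion gives the main question as "whether the patient-led goal-setting approach combined with PNE is more effective than MT in reducing pain intensity".

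The third arm is a pamphlet control: "Participants in the control group will receive no specific intervention". It appears in neither aim. The Discussion then adds it as a comparator: "Further objectives will be also to assess the effect of these two interventions on disability, quality of life, and psychosocial factors" against the control group.

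The Statistical analysis section has two branches. If the Shapiro-Wilk test accepts normality, a mixed-model ANOVA with group and time as fixed factors is fitted and "Bonferroni post hoc test will be used to find significant differences and compare the groups". If not, pairs of groups are compared by Mann-Whitney tests, with no correction stated. The significance threshold is 0.05. Neither branch ranks the contrasts or says how many there are.

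**The concern.** The aims rank the contrasts and the post hoc rule does not. If Bonferroni is spread over all three pairs, the one contrast that both aims name gets a third of the error rate, and two-thirds goes to contrasts that the article treats as further objectives.

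PNE versus MT compares two active packages that share the goal-setting component, so it is plausibly the smallest of the three differences and the one least able to bear a stricter threshold. A foreseeable outcome is that both packages beat the pamphlet while PNE versus MT misses 0.0167 but would have met 0.05. The sample size calculation gives no separate protection, because it reproduces as an overall group-by-time test rather than a test of this contrast.

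**Working it through.** **Inputs from the article.** Three arms, hence three pairs; 105 patients; 10% loss to follow-up; assessments at baseline and at 2, 4 and 12 months; threshold 0.05; effect size 0.25, labelled Cohen's d; power 95%; 15 per group calculated.

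**Assumptions.** Equal allocation, so 105/3 = 35 per arm, and 35 × 0.9 = 31.5 after loss; two-sided tests; one visit; error variance pooled over three groups; no baseline adjustment.

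**Step 1: the plan's own figure.** For the within-between interaction, λ = f²·N·m/(1 − ρ), with df (k − 1)(m − 1) and (N − k)(m − 1). Take k = 3, m = 4, f = 0.25, N = 45, and assume ρ = 0.5 and sphericity. Then λ = 0.0625 × 45 × 4/0.5 = 22.5 on 6 and 126 df, and power is 95.5%. The smallest adequate N is 44, so 15 per group reproduces. It does so with 0.25 taken as Cohen's f. A literal d of 0.25 (f = 0.125) would need 169 in total, or 57 per group. As a rough conversion, f = 0.25 corresponds to d = 2f = 0.5 for two groups, or d = f√6 = 0.61 for three equally spaced means.

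**Step 2: level per pair.** 0.05/3 = 0.0167.

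**Step 3: power for PNE versus MT.** Noncentral t with df = 3(n − 1) and noncentrality d·√(n/2). Losses are taken before rounding.

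| n per arm | d | power at 0.05 | power at 0.0167 | loss (points) |
|---|---|---|---|---|
| 35 | 0.25 | 17.9% | 8.7% | 9.2 |
| 35 | 0.50 | 54.5% | 37.0% | 17.5 |
| 35 | 0.61 | 71.8% | 55.2% | 16.6 |
| 35 | 0.676 | 80.0% | 65.3% | 14.7 |
| 35 | 0.87 | 95.0% | 88.4% | 6.6 |
| 31.5 | 0.25 | 16.6% | 7.9% | 8.7 |
| 31.5 | 0.50 | 50.1% | 33.0% | 17.2 |
| 31.5 | 0.61 | 67.1% | 49.9% | 17.3 |

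Hand check at n = 35, d = 0.5: noncentrality 0.5 × √17.5 = 2.09. The normal approximation gives Φ(2.09 − 1.96) = 55% and Φ(2.09 − 2.39) = 38%. The largest loss over all d is 17.6 points at either sample size.

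**Step 4: the same cost in other units.** The interval for PNE versus MT widens by 2.394/1.960 = 1.22. At 80% power the stricter level is equivalent to needing ((2.394 + 0.842)/(1.960 + 0.842))² = 1.33 times the patients for this contrast.

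**Step 5: what a better rule recovers.** With three groups, if one pair truly differs, at most one of the other two pairs can be equal. So once the smallest p-value is rejected at α/3, the other two can each be tested at α (Shaffer's step-down). Simulated at 35 per arm with PNE versus MT at d = 0.5, where Bonferroni gives 37%:

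- weaker package equal to control: about 44%;
- weaker package 0.3 SD better than control: 52%;
- weaker package 0.5 SD better than control: 54%.

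Family-wise error was about 4.4% with all groups equal. The error for PNE versus MT was at most 5.0% when those two were equal and both differed from control.

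**The case against.** Four points on the other side have weight.

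- **The control contrasts belong to the trial.** A reader might infer that Bonferroni over three pairs is an error, or that the control pairs are foreign to the question. The Discussion makes comparisons with control further objectives, including on disability, which is a primary outcome. Correcting over all pairs is therefore valid and conservative. What stands is the missing priority, not any failure of error control.
- **The size depends on the effect.** A reader might infer a flat loss of 14 to 18 points. At 35 per arm that holds only for d of about 0.37 to 0.69. At the literal 0.25 it is about 9 points, and at the stated 95% power about 7. At d = 0.25 even the uncorrected test has only about 18% power, so a null result there could usually not be blamed on the correction.
- **The 0.0167 is inferred.** The article gives no number of comparisons. All pairs is the natural reading, not a stated one.
- **The rule may not be reached for pain.** Pain is scored 0 to 10. When normal scores are rounded to integers (assumed means 3 to 6, SD 1.5 to 2.5), Shapiro-Wilk rejects in about 95% or more of samples of 105, but much less often in single groups of 35. The article does not say which unit is tested. In the Mann-Whitney branch the penalty disappears, and so does the protection.

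It can also be said that contrast hierarchies are often left to an analysis plan. Here, though, the article does fix a rule, and the point concerns that rule.

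**Conclusion.** The point holds as one of efficiency and priority. The post hoc rule in the normal-data branch does not follow the ranking in the aims. Read as all three pairs, it costs PNE versus MT about 7 to 18 points of power over the plan's own effect size and power and the medium effects that its sample size implies. If the planning effect was in fact Cohen's f, which is what reproduces 15 per group, the relevant figure is about 17 points.

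These sizes rest on 31.5 to 35 per arm, equal allocation, one visit and two-sided tests; the loss tends to zero for very small or very large differences. The documents do not support calling the rule invalid, nor saying that it will by itself leave the main question unanswered. The case for change is that a uniformly better rule is available at almost no cost, and that the threshold for the main contrast should not depend on the outcome of a normality test. Multiplicity over outcomes and visits is a separate matter and is not settled here.

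**What to change.** In the Statistical analysis section, replace the Bonferroni sentence with one of the following.

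**Option 1, all three pairs in one family.** *For each outcome and visit, the three pairwise group contrasts are tested by Shaffer's step-down procedure: the smallest p-value is compared with α/3 and, if it is rejected, each of the other two is compared with α.* This controls family-wise error over the pairs and rejects everything that Bonferroni rejects. Its cost is that matching simultaneous confidence intervals are less simple to report, and that recovery is only partial (about 44% against 37% at d = 0.5) if the weaker package is no better than control.

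**Option 2, follow the aims.** *PNE versus MT is the primary contrast and is tested at the full α given to that outcome and visit, with the matching confidence interval. The two contrasts with control are secondary and are tested with Holm's adjustment.* The error control for the secondary contrasts must be written down; demoting them without it would remove the only multiplicity protection that the article states. If error is to be controlled over all three pairs jointly, the control contrasts should be tested only after PNE versus MT is rejected. The cost is that the control contrasts lose equal standing, which agrees with the aims.

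Under either option, state the number of contrasts and apply the same rule in the Mann-Whitney branch. No new patients or data are needed.

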## Methods

### Study design and setting

This study is a three-arm single-blind RCT approved by the Ethics Committee in Research at Sport Sciences Research Institute of Iran (IR.SSRC.REC.1400.084) with the IRCT registration number IRCT20210927052616N1 and will be carried out in the Sport Medicine Laboratory of Kharazmi University of Iran. The CONSORT diagram for this study is provided in Fig. 1.

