### Outcome measures

All the outcome measures explained below were recorded at baseline (pre-test), 2 months post-test, and 4 and 12 months follow-up time points. The flow of the study is also provided in Table 3.

**Table 3 Tab3:** Schedule of enrollment, intervention, study visits, and assessments for all three study groups

Time point	Study period													
	Enrollment	Allocation	Patient-led goal-setting group with PNE				Patient-led goal-setting group with MT				Control group			
			Start	2 m	4 m	12 m	Start	2 m	4 m	12 m	Start	2 m	4 m	12 m
Enrollment														
Eligibility screen	*													
Informed consent	*													
Baseline assessment	*													
Allocation		*												
Intervention														
Patient-led goal-setting group with manual therapy							*	*	*	*				
Patient-led goal-setting group with PNE			*	*	*	*								
Assessments														
Start back			*				*				*			
QBPDS			*	*	*	*	*	*	*	*	*	*	*	*
NRS			*	*	*	*	*	*	*	*	*	*	*	*
SF_36			*	*	*	*	*	*	*	*	*	*	*	*
DASS			*	*	*	*	*	*	*	*	*	*	*	*
PSEQ			*	*	*	*	*	*	*	*	*	*	*	*
FABQ			*	*	*	*	*	*	*	*	*	*	*	*
Tampa Scale			*	*	*	*	*	*	*	*	*	*	*	*
PCS			*	*	*	*	*	*	*	*	*	*	*	*
RNPQ			*	*	*	*	*	*	*	*	*	*	*	*
CSI			*	*	*	*	*	*	*	*	*	*	*	*
Adverse events			*	*	*	*	*	*	*	*	*	*	*	*

*PNE* pain neuroscience education, *MT* manual therapy, *NRS* Numerical Rating Scale, *QBPDS* Quebec Back Pain Disability Scale, *PSEQ* Pain Self-Efficacy Questionnaire, *DASS* Depression Anxiety Stress Scale, *FABQ* Fear Avoidance Beliefs Questionnaire, *TSK* Tampa Scale for Kinesiophobia, *PCS* Pain Catastrophizing Scale, *CSI* Central Sensitization Inventory

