### Sample size estimation

Sample size has been estimated via G*Power 3.1.9.4 based on the therapy effects on pain and accounting for a 10% loss to follow-up after 4 and 12 months. An a priori power analysis was performed considering full factorial repeated measures and using a small effect size (Cohen’s *d*) of 0.25, confidence level (*α* = 0.05), and desired power (95%). The required sample size was calculated as 15 participants per group. Table 3 provides a schedule of enrollment, intervention, study visits, and all the assessments performed for all three study groups.

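### The main conclusion rests on an unadjusted comparison at each visit, so the baseline scores collected on every outcome add no precision to the deciding contrast

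*Protocol article*

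**What the plan says.** All of this comes from the protocol article; no SAP is shown.

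- **Deciding analysis** (Statistical analysis): "The main conclusion will be drawn from the unadjusted analysis without performing any subgroup analysis of primary and secondary outcomes".
- **Model terms** (same section): "Study group and time of assessment will be used as fixed factors and patients will be used as random factors". No baseline covariate is named, and no residual covariance structure is given.
- **Between-group contrast** (same section): the model is used "to examine the differences between groups in each time point (between group effects"), with Bonferroni post hoc tests.
- **Role of the pre-test** (same section): the model is also used to "compare the differences in scores related to each variable in the pre-test and post-test in each group (with-in group effects"). The pre-test score is therefore a level of time, that is, a response.
- **Data available** (Outcome measures): all outcomes are "recorded at baseline (pre-test), 2 months post-test, and 4 and 12 months follow-up time points". Table 3 shows NRS, QBPDS and every secondary scale at the start in all three groups.

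**The concern.** In a randomised trial with a continuous outcome measured before treatment, the baseline score is usually the best single predictor of the follow-up score. Putting it in the model as a covariate removes the part of the follow-up variance that it explains and corrects the contrast for whatever baseline difference chance produced. This plan collects those scores but fixes the deciding analysis as unadjusted.

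This is not a detail left open for an SAP. The protocol makes the choice in words, and an SAP that put baseline into the main analysis would contradict it. The main question, in Aims and Discussion, compares two active combinations, where the difference may be modest and precision matters most.

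**Working it through.** **The plan's own figure.** Sample size estimation gives 15 per group at 95% power for a repeated-measures design with effect size 0.25 and alpha 0.05. For a group-by-time interaction with k = 3 groups, m = 4 visits, f = 0.25, and assumed correlation 0.5 and sphericity:

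- λ = f²·N·m/(1−ρ) = 0.0625 × 45 × 4 / 0.5 = 22.5
- df = (k−1)(m−1) = 6 and (N−k)(m−1) = 126
- power = 95.6%

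So 45 in total, 15 per group, reproduces when 0.25 is entered as Cohen's f. (The text labels it d, which is a separate matter.) A correlation of 0.5 is thus one value that fits the stated calculation. The document states no correlation.

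**Inputs for the check.** Planned enrolment is 105 (Abstract). Equal allocation, giving n = 35 per arm, is assumed because no ratio is stated. Also assumed are SD = 1, a baseline-to-follow-up correlation r of 0.3, 0.5 or 0.6, a true difference d = 0.5 at a visit, and two-sided tests.

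**What the planned contrast is.** In a model with group, time and their interaction and with complete data, the estimated group difference at a visit is the difference between the two arm means at that visit. The baseline scores do not enter it.

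**Standard errors.**

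- Unadjusted: SD·√(2/n) = √(2/35) = 0.239. This is also the standard error of the chance difference between two arms at baseline.
- Adjusted for baseline: SD·√((1−r²)·2/n).

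| r | Variance factor 1−r² | Adjusted SE | Unadjusted trial size giving the same precision |
|---|---|---|---|
| 0.3 | 0.91 | 0.228 | 105/0.91 ≈ 115 |
| 0.5 | 0.75 | 0.207 | 105/0.75 = 140 |
| 0.6 | 0.64 | 0.191 | 105/0.64 ≈ 164 |

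A simulation of 20,000 trials at r = 0.5 with equal SDs agrees. The empirical SE was 0.241 unadjusted and 0.210 adjusted, and the adjusted test rejected 5.15% of the time under no effect.

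**Power at d = 0.5.** Noncentral t with 2×35−2 = 68 df and noncentrality (d/√(1−r²))·√(35/2). The one degree of freedom spent on the slope is ignored.

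| Analysis | Noncentrality | Power, 5% level | Power, 0.05/3 |
|---|---|---|---|
| Unadjusted | 2.092 | 54.1% | 36.5% |
| Adjusted, r = 0.3 | 2.193 | 58.0% | 40.2% |
| Adjusted, r = 0.5 | 2.415 | 66.3% | 48.8% |
| Adjusted, r = 0.6 | 2.615 | 73.2% | 56.6% |

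The last column applies if the Bonferroni step covers three pairwise comparisons.

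**Chance imbalance.** At r = 0.5, a baseline difference of one standard error carries about 0.5 × 0.239 = 0.12 SD into the follow-up difference. That is about a quarter of the assumed effect of 0.5.

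**The case against.** The strongest reply is that the planned contrast is pre-specified and valid. Randomisation makes the unadjusted difference unbiased, and its standard error already allows for chance imbalance. Nor is baseline thrown away: it is a response in the model, it enters the pre/post changes, and it informs incomplete patients under missing at random. All of that stands. To say that the plan discards its baseline data would go too far.

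A second reply is that the sample size section plans a full factorial repeated-measures design, which implies a group-by-time term, and that this term compares changes from baseline. This helps only in part. The change contrast has variance 2(1−r) relative to the raw difference, so the adjusted contrast still has (1−r²)/(2(1−r)) = (1+r)/2 of its variance, that is 65 / 75 / 80% at r = 0.3 / 0.5 / 0.6. The section in any case names differences at each time point as its between-group effect.

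Third, the power figures rest on d = 0.5 and on correlations that the document does not give, and 105 patients far exceed the calculated 45. That is fair. The figures show the size of the gain, not that the trial is underpowered.

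A reader might also infer three stronger criticisms, which the document does not support:

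- **The follow-up standard error is mis-stated and the 5% level is not kept.** This needs a patient random intercept as the only covariance term, and unequal SDs across visits. The protocol states neither, and the residual covariance may be given in an SAP. With equal SDs, simulation of the random-intercept model gives 5.3%. A baseline SD of 0.7 times the follow-up SD gives about 6.7%, but a ratio of 1.2 gives 3.9%, so the direction can reverse. The pain entry criterion makes a smaller baseline SD plausible for NRS. For QBPDS, the entry floor of 20 equals the stated scale minimum and so restricts nothing.
- **The treatment effect is diluted to three quarters.** That applies to a group main effect averaged over four visits, which is not the contrast the section names.
- **The estimate is biased by baseline imbalance.** It is not biased over repeated randomisations.

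**Conclusion.** The point holds as a loss of precision. The protocol fixes an unadjusted main analysis when a better-informed one is available from data it already collects. The variance given up is 9 / 25 / 36% at correlations of 0.3 / 0.5 / 0.6. At 0.5 it corresponds to about 35 further patients (140 against 105). These figures assume equal allocation, complete data and similar variances over visits; the power figures also assume d = 0.5. If baseline and follow-up were uncorrelated, nothing would be gained. The planned analysis is valid as it stands, and the document gives no ground to say that its type I error or standard error is wrong. The change is worth making, but its absence would not invalidate the trial.

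**What to change.** Replace the sentence on the unadjusted analysis. For each outcome, draw the main conclusion from a mixed model with:

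- the 2-, 4- and 12-month scores as responses;
- the baseline score of that outcome as covariate;
- group, visit and group-by-visit as fixed effects;
- preferably an unstructured within-patient covariance, so that variances and correlations may differ by visit.

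Report the unadjusted comparison as a sensitivity analysis. Keeping baseline as a response with its mean constrained to be equal across arms is an acceptable alternative.

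The cost is more than wording in an SAP. The choice is fixed in the protocol, recruitment began in October 2021, and the Protocol amendments section requires changes to be entered in the registry. The amendment should be dated and filed before the data are analysed, while the data analyst is still blinded as the Blinding section provides. No new data, patients or software are needed; SPSS fits this model.
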